## Methods/design

### Study design and schedule

RAPRASI is a clinical research study for participants with upper gastrointestinal malignancies (without metastatic disease) and who have controlled and stable kidney function. Radiotherapy treatment technique is according to local departmental protocols. Participants are being recruited as they present to the Department of Radiation Oncology, Sir Charles Gairdner Hospital (SCGH) in Perth, Australia, and to the Department of Radiation Oncology, Peter MacCallum Cancer Centre (PMCC) in Melbourne, Australia. The protocol has been approved by both institutional ethics committees. All patients are required to give written informed consent.

In addition to a baseline visit, timed to coincide with participants having a CT scan for the purpose of radiotherapy simulation, participants will have follow-up visits at 4, 12, 26, 52 and 78 weeks subsequent to the first radiotherapy treatment fraction. On each occasion they will undergo: a sequential ^99m^Tc-DMSA SPECT/CT (simultaneous SPECT and CT images), a GFR measurement (^51^Cr-EDTA clearance), a full blood count and assessment of blood urea and electrolytes.

The timing of SPECT/CT scans is intended to reveal i) acute and sub acute changes in total kidney function (GFR measurement) before and following radiotherapy, ii) information on kidney positioning before and following radiotherapy, and iii) the time-dependence of changes in regional kidney function and position (SPECT/CT scans) before and following treatment.

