### Data collection and quality assurance

This study will be conducted according to the Human Research Ethics Committee (HREC)-approved study protocol and the ‘Note for Guidance on Good Clinical Practice (CPMP/ICH/135/95) annotated with TGA comments’ (Therapeutic Goods Administration DSEB July [18]. The study will be performed in accordance with the NHMRC ‘National Statement on Ethical Conduct in Human Research’ (© Commonwealth of Australia 2007) and the ethical principles within the ‘Declaration of Helsinki’ (Revised 1996) [19].

Sir Charles Gairdner Hospital will act as the sponsor of this study at both the Peter MacCallum Cancer Centre and Sir Charles Gairdner Hospital in Perth, Western Australia. Standard medical care (prophylactic, diagnostic and therapeutic procedures) remains the responsibility of the patient’s treating physician.

The investigator is responsible for ensuring that no participant undergoes any study related examination or investigations prior to obtaining written informed consent. The investigator will explain the aims, methods, possible benefits and potential hazards before the participant gives consent. The participant will be given sufficient time to read the documentation, understand the project and have any questions addressed prior to signing the consent form. The participants will be advised that they have the right to withdraw their consent to participate at any time without any consequences.

Participant confidentiality will be protected at all times. In any resulting publication or presentation, no patients will be identified.

Records will be retained for 15 years post study completion in a locked facility, in accordance with TGA requirements. Access to participant study records will be limited to treating clinician, chief investigator, his/her nominated co-investigators and the local study co-ordinators.

Collation of data will yield the following for each participant:

– Local kidney function/response to therapy: regional change in SPECT signal intensity:

•from baseline to 4 weeks post start of radiotherapy

•from baseline to 12 weeks post start of radiotherapy

•from baseline to 26 weeks post start of radiotherapy

•from baseline to 52 weeks post start of radiotherapy

•from baseline to 78 weeks post start of radiotherapy

– Planned 3D Regional radiation dose distributions intended to be experienced during radiation treatment.

– Kidney function measure: GFR at baseline, 4, 12, 26, 52 and 78 weeks.

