### Statistical considerations

A target of 30 complete participant datasets has been set based on an assessment of anticipated patient numbers, recruitment and attrition rates, together with a power calculation of the number of datasets required to indicate a statistically significant variation in SPECT image intensity. A clinically significant difference would be a reduction of 20% from baseline to a follow-up imaging study [5]. In order to detect a conservative estimate of a 10% reduction, where the measurement error is 20% we would require a sample size of 33 (using a paired t-test with alpha = 0.05 and power = 80%; detecting 10.5% with 30 patients which is sufficient). With an anticipated 20% non-completion/attrition rate, allowance will be made for up to 40 recruited patients. Given the intensive data analysis required per patient dataset in this study, 30 datasets represents an upper-limit in terms of manageability.

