### Data analysis

To correlate the patterns of change in SPECT signal with time relative to delivered dose distributions, SPECT signal intensity will be used as a measure of local renal function – a change in this measure is an indication of ‘renal response’. This response needs to be correlated with regional radiation dose distribution. Planned 3D radiation dose distributions will be digitally registered with kidney functional changes in order to generate dose response models. The planning CT will be registered to the initial SPECT/CT data for definition of baseline kidney location and function. Subsequent SPECT/CT data (intensity-normalised according to administered nuclide activity) will be registered both using bone anatomy as well as SPECT intensity distribution providing registration of radiation dose distribution and SPECT signal. All imaging shall be performed with the patient in the same position on a flat-topped couch, allowing quantification of changes in kidney positioning in the abdomen relative to the planned dose distribution. Co-registrations will be made using the Velocity AI software [24]. Velocity’s deformable image registration will allow subsequent SPECT images to be deformable registered to the baseline SPECT/CT, on the basis of both CT anatomy and SPECT signal, and for all co-registered data sets to be deformable registered to the planned 3D dose distribution. This will allow subsequent SPECT images to be deformable registered to the baseline SPECT/CT, on the basis of both CT anatomy and SPECT signal, and all co-registered data sets to be deformable registered to the planned 3D dose distribution (or vice-versa), exported from the Treatment Planning System in DICOM-RT format. Applying these methods to data collected during the RAPRASI study will allow accurate spatial registration of regional changes in SPECT signal to planned radiotherapy dose. The method of registration to obtain correlated SPECT/dose is shown on Figure 2.

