iv. An export of co registered dose and SPECT information will be made for regions defined by whole kidneys, separately-identified medulla and cortex, baseline-image functional regions, and at varying spatial resolutions. Renal response patterns obtained from variations in SPECT and GFR shall be fitted to normal-tissue complication probability (NTCP) and equivalent uniform-dose (EUD) models, as previously undertaken by CI’s using estimated parameters [27,28]. Response indicators can be related to dose volume histogram (DVH) and dose-function histogram (DFH) data by maximum likelihood fitting to the parametric NTCP/EUD models. For this purpose, the freely available DREES code [29], developed in Matlab, will be utilised. Separate analyses will be undertaken using acute changes in SPECT signal (< 12 week images) as well as the long-term changes indicated by images taken at 52 or 78 weeks post-radiotherapy.

Examination of the predictive nature of response models will be made by establishing parameters based on the first 20 patient data sets, and utilising the models to predict SPECT signal changes on the subsequent 10 patients. In order to minimise parameter uncertainties however, final parameter values will be based on data for all patients.

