## Discussion

RAPRASI is a unique study combining functional radiological imaging with radiotherapy dose delivery for the assessment of regional radiation-induced kidney toxicity. The study focuses on a patient cohort which is poorly represented in clinical studies and for whom outcomes are known to be poor. Modern radiation therapy utilises intensive calculation processes and digitally driven beam delivery technologies to sculpt dose distributions in ways that were not previously possible. To take proper advantage of this technology it is necessary to understand how normal tissues are expected to respond to highly variable radiation dose distributions and how radiation dose may be sculpted to existing functional regions without detriment to the patient or the desired tumour dose. The information gained from the RAPRASI study, including models that allow prediction of temporal changes in kidney toxicity, will add to our current understanding of partial kidney radiation dose response to improve outcomes (including maximizing the preservation of function) of kidney dose response and tolerance to radiation.

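### Analysis iv: if functional regions are cut by intensity from the single baseline SPECT scan, that scan is both label and reference, and regression to the mean shifts their SPECT change

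*Protocol article*

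**What the plan says.** All statements are in the protocol article.

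- **One baseline scan.** Study design and schedule describes a single pre-treatment visit ("In addition to a baseline visit, timed to coincide with participants having a CT scan for the purpose of radiotherapy simulation") followed by scans at 4, 12, 26, 52 and 78 weeks. No repeat baseline is mentioned.
- **That scan defines function.** Data analysis states that "SPECT signal intensity will be used as a measure of local renal function", and that "The planning CT will be registered to the initial SPECT/CT data for definition of baseline kidney location and function".
- **That scan is also the reference for change.** Data collection and quality assurance lists "Local kidney function/response to therapy: regional change in SPECT signal intensity" for each follow-up scan, the last being "from baseline to 78 weeks post start of radiotherapy".
- **Functional regions come from the baseline image.** Data analysis, item iv, exports data for "regions defined by whole kidneys, separately-identified medulla and cortex, baseline-image functional regions, and at varying spatial resolutions". It then fits response patterns from SPECT and GFR to NTCP and EUD models by maximum likelihood.
- **Error assumed.** Statistical considerations: "where the measurement error is 20% we would require a sample size of 33", for a 10% reduction.

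The article describes no separate image for drawing the regions and no functional-class term or zero-dose offset in these fits. The one random effect it names, in item i, is for subject.

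**The concern.** When a noisy measurement sorts regions into classes and is then subtracted to obtain their change, the noise enters twice with opposite effect. A region that read high by chance is more likely to be labelled high, and its next reading tends to be lower. The reverse holds for a region that read low. More pixels or more patients do not remove this, because it is a bias and not a variance.

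The consequence would be a loss of signal in better-functioning tissue and a gain in poorer tissue that have nothing to do with dose. The article names no zero-dose offset, and NTCP and EUD forms as usually written have none. A class-level shift would then have to be absorbed by the fitted dose parameters. The planned check, fitting on 20 patients and predicting SPECT change in the next 10, would not expose it if regions are formed the same way in both sets, since the shift recurs in the test patients.

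The Discussion gives as motivation the need to know how "radiation dose may be sculpted to existing functional regions without detriment" to the patient. A false difference between functional classes bears on that question.

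**Working it through.** **Step 1. The plan's own figure.** Paired t-test, 10% reduction, SD 20%, two-sided alpha 0.05, power 80%.
- Normal approximation: n = (20 × (1.960 + 0.842) / 10)² = 31.4, so 32.
- Noncentral t: n = 34. Power at n = 33 is 79.5%.
- Detectable difference with 30 patients: 10.6% (stated 10.5%).

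The stated 33 lies between the two, so the figure reproduces with 20% as the SD of the paired difference. If 20% were the per-scan SD, the SD of the difference would be 20 × √2 = 28.3% and n would be 65. The reading that fits therefore implies 20 / √2 = 14.1% per scan, with equal, independent errors. This is a patient-level error; the article does not say how much of it is local.

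**Step 2. Inputs for the artefact.**
- Between-region CV of true baseline signal (T): not given; assumed 10, 20 or 30%.
- Local error per scan (E): not given; assumed 5, 10, 14.1 or 20%.
- Cut rule: not given; assumed a median split of baseline intensity.
- Normal, independent errors; no true change.

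**Step 3. Formula.** Reliability R = T² / (T² + E²). The expected distance of the upper half from the mean is √(2/π) = 0.798 observed SDs. So

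spurious shift = (1 − R) × 0.798 × √(T² + E²) = 0.798 × E² / √(T² + E²),

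downward in the half labelled high and equally upward in the half labelled low.

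Example, T = 20 and E = 14.1: 0.798 × 200 / √600 = 0.798 × 8.16 = 6.5% of mean signal.

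| T | E = 5% | E = 10% | E = 14.1% | E = 20% |
|---|---|---|---|---|
| 10% | 1.8 | 5.6 | 9.2 | 14.3 |
| 20% | 1.0 | 3.6 | 6.5 | 11.3 |
| 30% | 0.7 | 2.5 | 4.8 | 8.9 |

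(Percent of overall mean signal.) Relative to each class's own baseline mean, T = 20 gives −5.4% (high) and +8.1% (low) at E = 14.1, and −9.2% and +14.6% at E = 20.

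**Step 4. Simulation with no true change** (one million regions per setting, mean 100).
- T = 20, E = 14.1: −6.5 and +6.5. T = 20, E = 20: −11.3 and +11.3. Both agree with the formula.
- Averaged over all regions: zero to within 0.03.
- Labels taken from a second, independent baseline: both classes within 0.04 of zero.
- Dose unrelated to baseline signal: the dose slope within the high class is zero.
- Dose rising with true function (assumed: 22 Gy plus 0.5 Gy per percentage point of true signal above the mean, SD 10 Gy, limited to 0-45 Gy): a false slope of +0.3 to +0.4% of mean signal per Gy appears within the high class.

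No NTCP or EUD model was fitted. That those fits take up the shift is reasoning from their form, not a computed result.

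**The case against.** The strongest reply is that the mechanism is partly inferred. Item iv gives no threshold, split or smoothing rule, and a condensed article may leave delineation to the full protocol. If regions are contiguous or smoothed, selection noise shrinks. This stands, and it is why the point is conditional on an intensity cut. The condition is plausible: the article makes intensity the measure of function and takes the regions from the baseline image.

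The second reply is that item iv relates response to dose and states no contrast between functional classes, and that a dose slope within class is unbiased when dose is unrelated to baseline signal. This stands only in part. Without an offset, a fit confined to one class still has to explain that class's spurious shift through dose.

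Stronger readings are tempting, but the documents do not support them:

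- A reader might infer that all regional analyses are biased. Item i uses a uniform grid and item ii anatomical structures, so neither selects on baseline signal (unless medulla and cortex were separated by SPECT intensity). Whole-kidney averages cancel the effect. GFR, including the fits across functional regions in item iii, is a separate measurement.
- A reader might apply the full 20% error to pixels. It belongs to a patient-level paired test, and any scan-wide calibration part leaves ranks within a kidney unchanged and causes no such shift.
- A reader might conclude that better-functioning tissue will look more radiosensitive whatever the dose. That needs a known cut rule and a material local error, and the article gives neither.
- A reader might take the Discussion as a commitment to act on a class contrast. It is general motivation.

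**Conclusion.** The concern holds, within limits. If the functional regions in analysis iv are cut by SPECT intensity, the single baseline scan is used both to label them and to measure their change. The direction of the resulting error then follows for any non-zero independent local noise. The point is confined to the SPECT-change fits on those regions.

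The size is not determinable from the article. Over the assumed ranges it runs from 0.7 to 14.3% of mean signal, that is, from negligible to more than the 10% reduction used for the sample size. With 5% local error it is at most about 2%. It is worth settling before the functional-region fits are run, because the correction lies in the analysis alone.

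**What to change.** 1. **Preferred, where projection data allow.** Split the baseline counts. Use one half to define functional regions and the other as the reference for change. This breaks the link without any assumption about dose. It deals with counting noise; a local error shared by both halves of the same acquisition would remain and should be acknowledged.
2. **Otherwise.** Include functional class, as a class-specific zero-dose offset, in every SPECT-change fit on these regions. Base conclusions on dose dependence within class, not on the raw change of a class or on contrasts between classes. State that this is incomplete if dose correlates with baseline function, and report that correlation.
3. **Sensitivity check only.** Show the change in low-dose regions of the same class. It should not be subtracted as a correction: the Background reports that function depends on compensation by non-irradiated kidney, so signal there may truly rise, and subtraction would overstate the loss in irradiated tissue.
4. **Wording.** State how functional regions are cut and whether the image is smoothed first, so that the likely size can be judged.

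Cost: noisier half-count images under option 1, or a small loss of precision from the class term under option 2. The offset may need some adaptation of the parametric fits. No new scans or visits are needed.

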### Study hypotheses

An assessment of changes in total kidney function (using GFR measurement), regional kidney functional change (using SPECT imaging) and their correlation with radiotherapy dose delivery is within the means of currently available imaging, therapy and computational technology. The hypotheses being tested in RAPRASI are:

– Temporal variations in SPECT images of the kidneys correlate with patterns of radiation dose delivery in the kidneys.

– Models of kidney response developed from SPECT-response studies can be used to predict changes in kidney function as a result of radiation therapy.

The principal aim of RAPRASI is to obtain a better understating of kidney response when a patient is receiving radiotherapy for an upper-abdominal cancer. This will involve monitoring the spatial and temporal changes in kidney function for correlation with delivered three-dimensional radiation dose distribution. A more precise dose-volume response model for kidney will not only improve our current understanding but may permit further optimisation of radiation therapy techniques for upper-abdominal tumours.

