**Figure 2 F2:**
[figure not shown]
Diagram of the co-registration method.

This subsequent analysis of co-registered dose and image data will be undertaken in several ways:

i. Methods will be developed to assess dose-response correlations as a function of spatial position across each kidney (sampled at varying resolutions). Kidney volumes will be uniformly divided into regions on the three-dimensional (3D) grid defining image and spatially-registered radiation dose. t-tests and Wilcoxon signed-rank tests will be undertaken to determine regions with significantly different mean SPECT-signal intensities between time-points for each study participant. Mixed modelling with repeated measures (and random subject effect) will be conducted across all participant sets to examine the correlation of local radiation dose with SPECT signal changes, generating a map of dose-response change across all kidney volumes. Given a significant correlation, this will be extended to incorporate any revealed patterns of co-morbidity or adjuvant therapy as categorical variables.

ii. Dose-response correlations will then be examined according to structural and functional regions. Analysis i. will be repeated, but with regions defined according to kidney structure, with medulla, renal artery and cortex regions treated independently. This will also involve cross-correlation between these regions to examine inter-play that is likely to arise due to the influence of radiation effects on vascular structures.

iii. Spatio-temporal mathematical models of functional kidney dose-response will be implemented to relate regional kidney irradiation to the primary measure of total kidney function, GFR. These models, including percolation theory [25] and the critical functioning volume model of Rutkowska et al [26], will utilise the 3D radiotherapy dose distribution (both across each kidney and across individual functional regions) to fit model parameters using maximum likelihood estimation (MLE) methods. The statistical assessment of fitting will be made by assessment of parameter confidence intervals, and by undertaking an F-test of the residual sums-of-squares from MLE against that from MLE for a simple linear (single-parameter) dose-response model.

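### The only stated out-of-sample check of the response models predicts SPECT change in 10 patients; GFR models are assessed only in-sample, so patient-level cross-validation of both outcomes would test hypothesis 2 better

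*Protocol article*

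**What the plan says.** All references are to the protocol article.

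- **Study hypotheses.** The second hypothesis reads: "Models of kidney response developed from SPECT-response studies can be used to predict changes in kidney function as a result of radiation therapy".
- **Data analysis, opening.** SPECT intensity is taken as the measure of local renal function.
- **Data analysis, item iii.** Spatio-temporal models relate regional irradiation to "the primary measure of total kidney function, GFR". Their fit is assessed by parameter confidence intervals and an F-test against a one-parameter linear model.
- **Data analysis, item iv.** Response patterns from both SPECT and GFR are fitted to NTCP and EUD models by maximum likelihood, with separate analyses of early change and of change at 52 or 78 weeks.
- **Paragraph after item iv.** Prediction is examined by "establishing parameters based on the first 20 patient data sets, and utilising the models to predict SPECT signal changes on the subsequent 10 patients". To reduce parameter uncertainty, "final parameter values will be based on data for all patients".
- **Statistical considerations.** The study is sized for a paired change in SPECT intensity, with a target of 30 complete datasets. No size argument is given for the 20/10 division.
- **Data collection and quality assurance.** A participant enters the final analysis with only the baseline and 4-week scans. GFR is collected at baseline and at all five follow-up visits.

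**The concern.** Prediction is one of the study's two hypotheses, and the models are meant to inform treatment planning. The evidence that they predict in new patients rests on one division of the data, taken in order, with 10 patients in the test part. Patients are the independent units. Each contributes many kidney regions, but these are clustered within the patient, which is why item i uses a random subject effect. With 10 patients, a useful model may look poor by chance, or a poor one good.

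The held-out outcome is SPECT change alone. For GFR the plan offers goodness of fit on the fitting data. With multi-parameter models and about 30 patients, that is not evidence of prediction. The study could finish with a GFR model that has never been tried on a patient outside its own fit.

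**Working it through.** **1. The plan's own figure.** Inputs from Statistical considerations: alpha 0.05, power 80% and a paired t-test; an effect of 10 points; and, for the SD and the resulting number, "where the measurement error is 20% we would require a sample size of 33". Reading the 20% as the SD of the paired difference, with two-sided alpha:

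- Normal approximation: n = [(1.960 + 0.842) × 20 / 10]² = 31.4, so 32.
- Exact noncentral t: n = 34 (power 80.8%); n = 33 gives 79.5%.
- Detectable effect at n = 30: 10.6%, against 10.5% stated.

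The stated 33 is reproduced within rounding. It concerns detection of a mean SPECT change and says nothing about validating a model.

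**2. Precision of a 10-patient check.** The article gives no prediction-error SD. I assume 20%, the stated measurement error, and show a range. The patient is the unit. The 30-patient column stands for cross-validation over all datasets and is approximate, because cross-validated errors are correlated.

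| Quantity | Formula | 10 patients | 30 patients |
|---|---|---|---|
| Half-width, mean prediction error | t(0.975, n−1) × SD / √n | 2.262 × 20 / √10 = 14.3 points | 2.045 × 20 / √30 = 7.5 points |
| Same, SD 10% to 30% | as above | 7.2 to 21.5 | 3.7 to 11.2 |
| 95% interval for an RMSE of 20% | 20 × √(n / χ² quantile) | 14.0% to 35.1% | 16.0% to 26.7% |
| 95% interval for observed r = 0.7 | tanh[atanh(0.7) ± 1.96 / √(n−3)] | 0.13 to 0.92 | 0.45 to 0.85 |
| Smallest r different from zero at 5% | t / √(n−2+t²) | 0.63 | 0.36 |

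At SD 20%, the 10-patient half-width exceeds the 10% design effect. It is about 70% (14.3 / 20) of the clinically significant change, defined thus: "A clinically significant difference would be a reduction of 20% from baseline to a follow-up imaging study".

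**3. What 10 patients can detect.** By noncentral t at SD 20%, power against a 10-point systematic error is 29%. The error detectable with 80% power is 19.9 points, about the size of the clinically significant change.

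**4. Simulation, one value per patient.** Assumptions: true slope −1.2% per Gy, doses 2 to 30 Gy, residual SD 15%, one dose and one response per patient, R² scored against the training mean, 20,000 data sets.

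- 20/10 split: R² has SD 0.36, 95% range −0.70 to 0.67, negative in 18%.
- Leave-one-patient-out on the same 30: SD 0.14, range −0.01 to 0.54, negative in 3%.

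**5. Simulation, regional data.** Same slope, dose range and total residual SD, with 10 to 20 regions per patient, half or three-quarters of the residual variance between patients, and patient-varying slopes in some runs. R² is scored against the test mean. Regional doses and within-patient errors are independent, which is favourable to the split.

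- 20/10 split: SD 0.13 to 0.17, negative in 4 to 10%.
- Leave-one-patient-out: SD 0.05 to 0.06.

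The spread is much smaller than in step 4, but cross-validation remains more precise. Step 4 has the structure of a whole-patient outcome such as GFR; step 5 is nearer to the regional SPECT prediction that the plan describes.

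**6. Which outcome is tested where.**

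| Outcome | Fitted | In-sample assessment | Out-of-sample test stated |
|---|---|---|---|
| Regional SPECT change | items i, ii, iv | yes | yes, 10 patients |
| GFR change | items iii, iv | yes (confidence intervals, F-test) | none |

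For change at 52 or 78 weeks the test set could fall below 10, because the minimum for analysis is baseline plus 4 weeks.

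**The case against.** The strongest reply is that this is an exploratory observational study, limited to 30 datasets on stated grounds of manageability, and that a time-ordered hold-out is a recognised design. Preferring cross-validation is partly a matter of method. That is fair, and it is a reason to allow the split to stay alongside a more precise check.

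Several stronger readings are tempting but not supported:

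- *Ten patients cannot judge any model.* A bias of about 20 points would be found with 80% power at SD 20%, so gross failure is visible.
- *The split cannot rank the competing models.* The article does not say that it will. It describes only an examination of predictive behaviour.
- *GFR is never tested.* It is fitted in items iii and iv, and formally assessed in item iii. What is absent is any out-of-sample test.
- *Hypothesis 2 goes untested.* It speaks of kidney function without naming GFR, and SPECT is defined as local function, so the hold-out does address its regional part.
- *Refitting on all patients invalidates the check, or a third of the data is wasted.* Refitting after validation is standard, the article gives its reason, and the final parameters use everyone. Cross-validation also evaluates fits other than the final one.
- *R² would be negative in 18% of such studies.* That figure belongs to one value per patient, not to the planned regional data.

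A full protocol or analysis plan may add performance measures; their absence from the article is not part of this point. The split and its SPECT-only target are stated outright.

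**Conclusion.** The point holds in a limited form. The one stated out-of-sample check uses 10 patients and SPECT change, and GFR models are judged only in-sample. Hypothesis 2 is thus tested weakly for regional function and not out of sample for total function.

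The size of the imprecision is roughly a doubling of the half-width for mean prediction error compared with using all 30 datasets (14.3 / 7.5 = 1.9). This ratio does not depend on the assumed SD; the absolute figures do. The correlation of 0.7 is illustrative, and the simulation results depend on the assumed slope, doses and residual structure. The direction, with cross-validation more precise, was the same for whole-patient and regional data.

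This is a worthwhile, inexpensive improvement. It does not invalidate the study.

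**What to change.** Replace or supplement the 20/10 split with one of the following, over all analysable patients:

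- leave-one-patient-out or repeated k-fold cross-validation at patient level, keeping all regions of a patient in the same fold; or
- bootstrap optimism correction, resampling patients.

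Repeat every model-building step within each fold or resample. Report prediction error and calibration for regional SPECT change and for GFR change at 52 and 78 weeks, with the number of patients contributing at each time. Keep the final parameter fit on all patients.

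The cost is analysis-plan wording and computing time. No new patients, scans or visits are needed, since GFR is already measured at every visit. If the split is replaced rather than supplemented, the purely temporal hold-out is lost; keeping it as a secondary check avoids that.
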